## Methods/design

### Study design

This is a single-center, evaluator-blind, randomized controlled trial conducted at Shanghai Municipal Hospital of Traditional Chinese Medicine in China. All eligible participants will be randomly divided at a ratio of 1:1 into Tai Chi group (TC group) (1x/week for 12 weeks) and attention control group (AC group) with health education and stretching program (1x/week for 12 weeks) with a follow-up period of 6 weeks. The primary outcome is the change of Western Ontario and McMaster Universities (WOMAC) pain subscale at week 12 compared with baseline. Secondary outcomes include WOMAC pain subscales at other time-points, stiffness and function subscales, data from isokinetic dynamometry, gait analysis with electromyography (EMG), and a 36-item short form health survey (SF-36). The daily dose of pain-relieving medication will also be recorded. All outcomes will be assessed at baseline (week − 1) and at the end of the intervention (week 12). In addition, WOMAC and SF-36 will also be assessed at 6^th^ week of the intervention (week 6) and at the end of follow-up (week 18). The design of this clinical trial will strictly follow the Consolidated Standards of Reporting Trials (CONSORT) Statement and Standard Protocol Items: Recommendations for Interventional Trials (SPIRIT) [30]. The trial flowchart is presented in Fig. 1, and the study design schedule is shown in Table 1; Fig. 1.

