### Sample size calculation

The calculation of sample size is based on hypothetical changes in WOMAC pain subscale at week 12. We are using the results of a randomized controlled trial [26] to formulate expected effects. We hypothesized that a 118-point improvement in WOMAC pain subscale occurred in the Tai Chi group compared to the attention control group. A sample size of 40 per group provides 90% power to detect these differences using a 2-sided significance level of 0.05 through PASS software (version 15.0.5) and considering the expected dropout rate of 20%, the study will require 100 patients in total.

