### Outcome measurement

#### Primary outcome

The primary outcome is the change in WOMAC pain subscale between baseline and week 12. The self-reported WOMAC pain subscale is aimed to assess pain intensity when walking on a flat surface, going up or down stairs, lying in bed at night, sitting or lying, and standing upright [31]. WOMAC has three subscales evaluating joint pain (score range, 0-500), stiffness (0-200) and physical function (0-1700), respectively, with higher scores indicating more severe disease. The visual analogue scale (VAS) version of WOMAC is a disease-specific, self-administered instrument and widely used in clinical trials with satisfactory reliability and validity [32–34].

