#### Data collection and statistical analysis

A standardized CRF has already been designed prior to the study, including participants’ characteristics, outcome measures, evaluation time points, adverse events, etc. Two independent data administrators, who are blind to group allocation, will check CRF data and double-enter it into an Excel database once a week. Raw data can be shared by contacting researchers if requested within 6 months of completion of the trial.

A complete analysis set (FAS) is based on the ITT principle, which includes all qualified participants who have received at least one intervention and at least one outcome measurement. Missing data will be imputed through last observation carried forward (LOCF) methodology. A Per-Protocol Set (PPS) will also be used to analyze those who completed the trial without major protocol violations as an auxiliary set. The analysis will be based on the intention-to-treat principle and include all randomly assigned participants receiving interventions. Statistical analysis will be carried out by an independent statistician using SPSS version 26.0. Descriptive characteristics will be presented as mean ± standard deviation or median (interquartile range, IQR) for continuous variables and n (%) for categorical variables. Analysis of variance (ANOVA) or Chi-square test will be used to verify baseline balances of variable characteristics between groups, as appropriate. Changes in repeat outcomes over time will be compared by linear-mixed effects model with group and visits as fixed effects. A Bonferroni correction will be used for multiple comparisons. Statistical significance will be set at a 2-tailed p-value of 0.05.

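### The stated model does not adjust week-12 change in WOMAC pain for baseline pain, and the planned baseline tests are no substitute: some precision is given up at no saving

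*Protocol article*

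**What the plan says.** Under Outcome measurement, the endpoint is a change score: "The primary outcome is the change in WOMAC pain subscale between baseline and week 12". Table 1 schedules WOMAC pain at week -1 and at weeks 6, 12 and 18, so a baseline value is planned for everyone.

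The section Data collection and statistical analysis makes two statements that matter here. On baseline: "Analysis of variance (ANOVA) or Chi-square test will be used to verify baseline balances of variable characteristics between groups, as appropriate". On the outcome model: a "linear-mixed effects model with group and visits as fixed effects". No baseline covariate, analysis of covariance or constraint on the baseline means appears anywhere in the article, and the result of the balance tests is not linked to any later step.

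The section on sample size gives the planning figures: "We hypothesized that a 118-point improvement in WOMAC pain subscale occurred in the Tai Chi group compared to the attention control group", and "A sample size of 40 per group provides 90% power to detect these differences using a 2-sided significance level of 0.05". It states neither an SD nor a baseline to week-12 correlation.

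**The concern.** Participants are randomised 1:1, so any baseline difference between the groups is due to chance. A baseline p-value therefore tests a hypothesis already known to be true. A non-significant result does not show balance, and a significant one does not show a fault.

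What protects the comparison is adjustment for the baseline value of the outcome, and the stated model has none. Change from baseline usually remains negatively correlated with the baseline value, because people who start high tend to fall further. If one group happens to start higher, part of its larger fall is regression to the mean and stays in the estimated effect. The variation in change that baseline could explain also stays in the error term. At stake are the width of the confidence interval for the primary contrast and its robustness to an unlucky allocation.

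**Working it through.** **Inputs from the article.** Difference 118 points, 40 per group analysed, 90% power, two-sided 0.05, 20% dropout, 1:1 allocation.

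**Inputs assumed, because the article gives none.** Correlation rho between baseline and week-12 pain of 0.3 to 0.7; equal SDs at the two visits (relaxed in step 4); the 40 per group based on the SD of unadjusted change.

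**1. The plan's own figure.** The dropout step reproduces: 40/(1 - 0.20) = 50 per group, 100 in total. The 40 itself cannot be reproduced without an SD, but it can be solved backwards. With the normal approximation, 90% power requires 118/(SD × √(2/40)) = 1.960 + 1.2816 = 3.2415, so SD = 118/(3.2415 × 0.2236) = 162.8 (about 160.8 with the t distribution). The standardised effect is about 0.72 to 0.73.

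**2. Adjusted against unadjusted, equal SDs.** Let σ be the SD at one visit.

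- Variance of change: 2σ²(1 - rho)
- Residual variance after baseline adjustment: σ²(1 - rho²)
- Ratio: (1 + rho)/2

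Power at 40 per group is Φ(3.2415/√ratio - 1.960).

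| rho | variance ratio | CI narrower by | power at 40 per group | n per group for 90% |
|---|---|---|---|---|
| 0.3 | 0.65 | 19% | 98.0% | 26 |
| 0.5 | 0.75 | 13% | 96.3% | 30 |
| 0.7 | 0.85 | 8% | 94.0% | 34 |

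A simulation of 20,000 trials with 40 per group gave variance ratios of 0.66, 0.76 and 0.86. Both estimators averaged about 118.

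**3. What the balance test lets through.** At 50 per group, a baseline difference of up to 1.96 × √(2/50) = 0.39 SD is non-significant. A true imbalance of 0.3 SD would be flagged with probability of only about Φ(0.3/√(2/50) - 1.96) = Φ(-0.46) = 0.32. A realised difference of 0.39 SD shifts the expected change contrast by (1 - rho) × 0.39 × σ. With σ = 162.8/√(2(1 - rho)), σ is 138, 163 and 210 at rho 0.3, 0.5 and 0.7, and the shift is about 38, 32 and 25 points. That is 32%, 27% and 21% of 118. These are shifts at the largest imbalance the test would pass, not typical ones.

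**4. Unequal SDs.** Let k be the week-12 SD divided by the baseline SD. The ratio becomes k²(1 - rho²)/(1 + k² - 2·k·rho). The denominator equals k²(1 - rho²) + (1 - k·rho)², so apart from the small cost of estimating a slope, adjustment does not lose precision, and it gains nothing when k·rho = 1. At an assumed k of 1.3:

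- rho 0.3: 1.538/1.910 = 0.81, power about 95%
- rho 0.5: 1.268/1.390 = 0.91, power about 92%
- rho 0.7: 0.862/0.870 = 0.99, power about 90%

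A k above 1 is plausible here, because the entry rule (at least one pain item of 40 or more) cuts off the low end of baseline pain. With equal SDs, rho = 0.9 gives a ratio of 0.95.

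**The case against.** The best defence is that the article is a summary. Its sentence on the model names no random effects, interaction or covariance structure either, and a full analysis plan may list covariates. That lowers the certainty but does not remove the point: the article does list fixed effects, and baseline is not among them.

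A second defence is that baseline may be one of the visits. This does not supply the adjustment. With complete data and unconstrained group-by-visit means, the week-12-minus-baseline contrast is simply the raw difference in change. If the model had only main effects of group and visit with baseline included, the group term would average over four visits, and a constant post-baseline effect of 118 would appear as 118 × 3/4 = 88.5. Only constraining the baseline means to be equal does the work of a covariate.

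It also stands that the comparator in the working is a plain week-12 change score. The article does not say whether the mixed model's response is change or the raw score, so the percentages illustrate the gain and do not measure this plan's loss.

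A reader might infer four stronger things that the article does not support:

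- **That the planned comparison is biased.** It is not, on average over randomisations; the shift in step 3 is conditional on a realised imbalance.
- **That 100 participants are too few.** Nothing here shows that.
- **That the same loss applies to strength, gait and the other secondary outcomes.** Their correlations and SDs are not given, and strength and gait are measured only twice, so the repeated-measures model may not be meant for them.
- **That adjustment would make up for power lost to clustering within classes.** The article gives no intraclass correlation, and an individual's baseline score does not remove class effects that arise during the training.

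Finally, the baseline tests change no estimate or p-value for the outcomes. On their own they are a reporting matter.

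**Conclusion.** The point holds as a low-cost improvement, not as an error that undermines the primary result. The stated model leaves out a prognostic covariate scheduled for every participant, and the planned tests of balance cannot stand in for it.

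With equal variances and rho between 0.3 and 0.7, the variance of the primary contrast would be 15% to 35% lower with adjustment. That conclusion does not depend on the SD. The move from 90% power to about 94% to 98% further requires that the 40 per group rests on the SD of unadjusted change. If it rests on another SD, the ratio is unchanged but the starting power is not 90%. With a larger spread at week 12 or a high correlation, the gain shrinks and may be close to nil. Protection against chance imbalance shrinks with it, because both depend on how far the regression slope lies from 1.

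**What to change.** - **Repeated outcomes (WOMAC subscales, SF-36).** Prespecify a model for the post-baseline visits with group, visit, group-by-visit, the outcome's baseline value and baseline-by-visit. Alternatively, keep baseline in the response and constrain its mean to be equal across groups. State that the week-12 group contrast for WOMAC pain is the primary result. The group-by-visit term is needed, since a baseline covariate alone does not yield a week-12 contrast.
- **Outcomes measured only at baseline and week 12 (strength, gait).** Use analysis of covariance with the baseline value as covariate.
- **Baseline characteristics.** Replace the ANOVA and chi-square tests with a descriptive table by group.

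The cost is a few sentences of analysis text, with no new measurements and no change to the sample size. Recruitment has begun, so the change should be dated and fixed before anyone sees outcome data by group; the choice of covariates then cannot follow from the observed imbalances. If the full analysis plan already contains this adjustment, it is enough to align the published description with it.

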#### Secondary outcome

**WOMAC** WOMAC pain subscale assessed at week 6 and 18, stiffness and physical function subscales assessed at week 6, 12 and 18 will be evaluated as secondary outcomes.

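### The mixed model lists only group and visit as fixed effects, so its group coefficient averages over visits and does not estimate the primary outcome, the week-12 change in WOMAC pain

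*Protocol article*

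**What the plan says.** The Primary outcome section fixes the target: "The primary outcome is the change in WOMAC pain subscale between baseline and week 12". The Sample size calculation section uses the same time point: "The calculation of sample size is based on hypothetical changes in WOMAC pain subscale at week 12". It assumes a between-group difference of 118 points on the 0 to 500 pain scale and states that "A sample size of 40 per group provides 90% power to detect these differences using a 2-sided significance level of 0.05".

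The Study design section and Table 1 place WOMAC at baseline (week −1) and at weeks 6, 12 and 18. The Secondary outcome section makes WOMAC pain at weeks 6 and 18 secondary.

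The section Data collection and statistical analysis gives one between-group method for outcomes: "Changes in repeat outcomes over time will be compared by linear-mixed effects model with group and visits as fixed effects". It continues with "A Bonferroni correction will be used for multiple comparisons" and a two-tailed 0.05 level. ANOVA and the chi-square test are named only for baseline balance. The article states no group-by-visit interaction, no week-12 contrast and no separate test of the week-12 change.

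**The concern.** A model with group and visit as its only fixed effects has a single treatment parameter, and that parameter is the same at every visit. A week-12 contrast taken from the fitted model is therefore just the pooled group coefficient, and pairwise comparisons computed afterwards cannot recover a visit-specific difference.

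Two things then enter the primary test that should not. One is weeks 6 and 18, which the article makes secondary: week 6 falls in mid-intervention and week 18 six weeks after the intervention ends. The other is baseline, if it is one of the response visits, where randomisation makes the expected difference zero. The primary p-value would then answer a different question from the one that the trial declares and is sized for. The term that carries the declared question, the interaction, is the one that the list of fixed effects leaves out.

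**Working it through.** **Inputs from the article.** Difference 118 points at week 12; 40 per group; 90% power; two-sided 0.05; 20% dropout; 100 in total; four WOMAC visits.

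**Inputs assumed here.** The article gives no SD, no between-visit correlation and no effect at weeks 6 and 18. I assume compound symmetry with correlation ρ = 0.5 and try four effect patterns. All four have 118 at week 12.

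**Step 1: the plan's own figures.** The dropout step reproduces: 80 / (1 − 0.20) = 100. The 40 per group cannot be reproduced without an SD, but it can be inverted. A two-sample t-test with 40 per group has 90% power at a standardised difference of 0.734, so the implied SD of change is 118 / 0.734 ≈ 160.8.

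**Step 2: what the group coefficient estimates.** Let Δ0, Δ6, Δ12, Δ18 be the group differences at each visit, with Δ0 = 0 by randomisation. For complete data with a random intercept, the main-effects coefficient is the equal-weight mean:

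- baseline among the response visits: (0 + Δ6 + Δ12 + Δ18) / 4
- change from baseline as response: (Δ6 + Δ12 + Δ18) / 3

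The primary target is Δ12 − Δ0 = 118.

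**Step 3: variances.** With change SD s_c = 160.8, the SD at a single visit is s = s_c / √(2(1 − ρ)) = 160.8 at ρ = 0.5.

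- Four-visit mean: s²(1 + 3ρ)/4 = 0.625 s², SD 127.1.
- Mean of three changes: s²[(1 + 2ρ)/3 + 1 − 2ρ] = 0.667 s², SD 131.3.

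**Step 4: results**, 40 per group, two-sided 0.05, noncentral t:

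| Effect at weeks 6/12/18 | Coefficient, baseline in response | Power | Coefficient, change as response | Power |
|---|---|---|---|---|
| 118/118/118 | 88.5 | 87% | 118 | 98% |
| 59/118/118 | 73.75 | 73% | 98.3 | 91% |
| 59/118/59 | 59 | 54% | 78.7 | 75% |
| 0/118/0 | 29.5 | 18% | 39.3 | 26% |

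The week-12 contrast from a model with the interaction targets 118 in every row, with 90% power.

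**Step 5: sensitivity to the correlation.** With the change SD held at 160.8, the change-score columns do not depend on ρ. With baseline in the response they do: for the constant effect, power is 95%, 87% and 74% at ρ = 0.4, 0.5 and 0.6.

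**Step 6: simulation.** With 8,000 simulated participants, the main-effects coefficient was 88.7, 74.1, 58.4 and 29.4 (baseline in response) and 119.6, 100.0, 82.8 and 38.1 (change), in the row order above. The interaction model's week-12 contrast lay between 117 and 125 in all four, around the true 118. Its standard error is about 160.8 × √(2/4000) = 3.6, so this spread is sampling error.

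**The case against.** The best reply is that the sentence is shorthand. It covers all repeated outcomes at once in a condensed article, and its stated purpose, comparing changes over time, is what a group-by-visit term does. It does not exclude an interaction, and an analysis plan that is not shown may contain one. This stands as a caution about what the sponsor intends: the text does not prove that a pooled test is planned. It does not remove the point, because the article does specify fixed effects, and the ones it lists do not estimate its own primary outcome.

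A reader might infer that power is certainly lost. The documents do not support that. With change as the response, which the sentence's wording permits, baseline is not a response visit, and a constant effect gives about 98% power. The pattern 59/118/118 gives 91%. Even with baseline in the response, a constant effect gives 95% at correlation 0.4. Losses appear under other assumptions, but none of these assumptions is in the article.

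A reader might also infer that the Bonferroni sentence lowers the primary test to 0.05/3 = 0.0167. That does not follow either. The article does not name the family, the primary outcome is one comparison of two arms at one time point, and weeks 6 and 18 are labelled secondary.

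**Conclusion.** The point holds as a mismatch between the stated model and the stated primary outcome. Fitted as listed, the model tests a visit-averaged group difference. That average equals the week-12 difference in change if change is the response and the effect is the same at weeks 6, 12 and 18. Otherwise the two agree only by an arithmetical coincidence, such as weeks 6 and 18 averaging exactly to the week-12 value.

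The size depends on the assumed pattern and response: a target of 29.5 to 118 points where the trial is sized for 118, and power of about 18% to 98% where 90% is stated. The power range is illustrative. It rests on the back-calculated SD, compound symmetry, correlation 0.5 and complete data, and it supports no claim of a net loss. The mismatch itself needs none of these assumptions. Because it decides what the primary p-value means, it should be settled before anyone sees unblinded data.

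**What to change.** Replace the model sentence with text to this effect: WOMAC pain will be analysed by a linear mixed model with group, visit (categorical) and group-by-visit interaction as fixed effects; the single primary test is the between-group contrast in change from baseline to week 12, at two-sided 0.05; the week-6 and week-18 contrasts from the same model are secondary. The sponsor may add, for clarity, that the Bonferroni correction applies to the secondary comparisons.

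If an interaction is already intended, this only makes the public text say so. The cost is one or two sentences. No further data are needed, the total stays at 100, and SPSS, the software already named, fits the model.

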#### Measures of muscle strength

Maximal voluntary muscle strength of extensor and flexor will be measured by isokinetic dynamometry at angular velocities of 30 deg/s and 60 deg/s (Biodex System 4 Pro, Biodex Medical System, NY, USA) at baseline and week 12. Before the test, the patient will be comfortably positioned on dynamometry with the hip at 85 deg and the knee at 90 deg flexion. The shin will be placed and strapped in the foot adapter and the rotation axis will be aligned with the flexion and extension axis of the knee. The patient will then be instructed to perform flexion and extension according to his or her physiological capability within the range of motion (ROM) of the knee joint during a 5-minute warm-up period to familiarize himself with the test procedure. A gravitational correction will be applied to negate the influence of the gravity-effect torque on the test data. During the formal test, each patient will be required to fold their arms across their chest and given verbal encouragement in an attempt to achieve a maximum level of effort. The angular velocities of 30 deg/s and 60 deg/s will be applied to two sets of five maximal knee extensions and flexions with a 60-second rest interval between sets, which are chosen according to previous studies [22, 35]. The mean of each set will be selected as maximal isokinetic muscle strength. The peak torque (PT), peak work (PW), total work (TW), peak torque angle (PTA) and average power (AP) of quadriceps were recorded for each velocity.

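### Optional efficiency gain: Holm's step-down procedure could replace the single-step Bonferroni correction for non-primary comparisons at the same 5% family-wise error

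*Protocol article*

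**What the plan says.** The multiplicity rule is one sentence in the protocol article, under Data collection and statistical analysis: "A Bonferroni correction will be used for multiple comparisons". It comes directly after the model statement, "Changes in repeat outcomes over time will be compared by linear-mixed effects model with group and visits as fixed effects", and directly before "Statistical significance will be set at a 2-tailed p-value of 0.05". Neither a family nor a number of comparisons is given, and no step-down version is mentioned.

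There is one primary comparison: "The primary outcome is the change in WOMAC pain subscale between baseline and week 12". The sample size section powers only that comparison: "A sample size of 40 per group provides 90% power to detect these differences using a 2-sided significance level of 0.05".

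Several sets of non-primary comparisons could need a correction:

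- **WOMAC** (Secondary outcome): "WOMAC pain subscale assessed at week 6 and 18, stiffness and physical function subscales assessed at week 6, 12 and 18". That is 2 + 3 + 3 = 8 outcome-by-visit comparisons.
- **Quadriceps strength** (see Measures of muscle strength in the article): "The peak torque (PT), peak work (PW), total work (TW), peak torque angle (PTA) and average power (AP) of quadriceps were recorded for each velocity". Five parameters at two velocities make 10 comparisons at week 12.
- **SF-36**: eight dimensions.

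The article does not say which of these sets, if any, the correction covers.

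**The concern.** Single-step Bonferroni tests each of m comparisons at 0.05/m, whatever the other comparisons show. Holm tests the smallest p-value at 0.05/m, the next at 0.05/(m − 1), and so on up to 0.05, and stops at the first failure. Both procedures hold the family-wise error at 5% under any correlation. Only the first threshold is the same, so Holm can never reject fewer comparisons and may reject more.

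The difference is largest when several true effects sit in one family. The trial's hypotheses run that way: pain, quadriceps strength and physical function are all expected to improve. The sample size is set for WOMAC pain alone, so any comparison that falls under the correction has no power reserved for it. With the single-step rule, some true effects could be missed for the sake of error protection beyond the 5% the plan asks for.

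**Working it through.** **Inputs from the article.** 40 per group, 90% power, two-sided 0.05, a 118-point difference, 20% dropout and 100 patients in total (Sample size calculation).

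**Inputs assumed, because the article does not give them.** Family size m = 3, 5 or 10; number of real effects k; correlation 0 or 0.5 between test statistics; standardised effect d = 0.5, or the value implied for the primary outcome.

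**Step 1: the plan's own figures.** The total is reproduced: 2 × 40 / (1 − 0.20) = 100. The 40 per group cannot be checked because no standard deviation is given. Solving back with the normal approximation:

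d = (1.960 + 1.282) / √(40/2) = 3.242 / 4.472 = 0.725

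This implies a standard deviation of 118 / 0.725, about 163 points. An exact t-test calculation gives d of about 0.73.

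**Step 2: power of one comparison under Bonferroni.** Power = Φ(d√20 − z), where z is the upper 0.025/m point of the standard normal distribution.

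| m | level 0.05/m | d = 0.5 | d = 0.725 |
|---|---|---|---|
| 1 (unadjusted) | 0.05 | 60.9% | 90.0% |
| 3 | 0.0167 | 43.7% | 80.2% |
| 5 | 0.01 | 36.7% | 74.7% |
| 10 | 0.005 | 28.4% | 66.8% |

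**Step 3: Bonferroni against Holm by simulation.** 200,000 sets of correlated z-statistics per setting, 40 per arm. Average power per true effect at correlation 0.5, Bonferroni → Holm:

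| m | real effects | d = 0.5 | d = 0.725 |
|---|---|---|---|
| 3 | all 3 | 43.8% → 50.6% | 80.2% → 86.7% |
| 5 | all 5 | 36.7% → 44.3% | 74.7% → 83.7% |
| 10 | all 10 | 28.3% → 35.3% | 66.7% → 78.2% |
| 5 | 2 | 36.5% → 37.8% | 74.7% → 76.3% |
| 10 | 5 | 28.5% → 30.5% | 66.8% → 70.2% |
| 5 | 1 | 36.9% → 37.0% | 74.7% → 74.7% |
| 10 | 1 | 28.4% → 28.4% | 66.7% → 66.8% |

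The gains at correlation 0.5 are:

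- **All effects real and equal:** from 86.7 − 80.2 = 6.5 points to 78.2 − 66.7 = 11.5 points.
- **About half real:** from 37.8 − 36.5 = 1.3 points to 70.2 − 66.8 = 3.4 points.
- **One real:** about 0.1 point.

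At zero correlation the all-real range widens. For m = 10 it runs from 32.7 − 28.4 = 4.3 points (d = 0.5) to 81.3 − 66.8 = 14.5 points (d = 0.725).

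**Step 4: error control.** With no real effects the simulated family-wise error was the same for both methods: 4.9% at m = 10 with zero correlation, 3.9% with correlation 0.5. With 5 of 10 effects real (d = 0.725, correlation 0.5) it was 2.2% for Bonferroni and 3.3% for Holm. Holm spends some of the unused allowance and stays under 5%.

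**Step 5: how much of the loss Holm regains.** For m = 10, all real, d = 0.725, correlation 0.5, power is 90% unadjusted, 66.7% with Bonferroni and 78.2% with Holm. Holm regains 11.5 of 23.3 points, about half. The chance of at least one rejection is essentially the same for both methods (97.0% here).

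**The case against.** The strongest reply is that nothing here is wrong. Bonferroni is valid under any dependence, is widely understood, and has simultaneous confidence intervals that match its tests. Holm has no simple equivalent, so Holm-adjusted p-values may sit beside intervals that disagree with them. Preferring the simpler pair is defensible. That stands, and it is why this is a suggestion and not a correction. The article promises no simultaneous intervals, so the loss is small, but it is real.

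A reader might go further and infer that the plan sacrifices power on quadriceps strength, SF-36 and physical function in particular. The article does not support this. The Bonferroni sentence follows the mixed-model sentence and may refer only to visit contrasts within one outcome. On that reading the SF-36 dimensions and the strength parameters are never pooled. Strength is measured only at baseline and week 12, so its treatment effect might not be corrected at all.

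A reader might also take the largest gains as the expected ones. Those assume that every comparison in the family has the same true effect, and the 0.725 is back-solved from the primary outcome, with nothing in the article to carry it over to secondary outcomes. Nor does Holm restore all the lost power, as the last step of the working shows.

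What survives is narrower: on whatever family of two or more comparisons was meant, Holm is never less powerful at the same stated error.

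**Conclusion.** The point holds as an optional, low-cost improvement. The plan commits to a valid correction, and a uniformly at-least-as-powerful version exists at the same two-sided 5% family-wise error with no added assumption. It would be wrong to call the Bonferroni sentence an error or a contradiction, or to say that it demonstrably costs the secondary outcomes a known amount of power.

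The benefit in this trial cannot be fixed, since the family, the secondary effects and the correlations are all unstated. Under the assumptions in the working it lies between practically zero and about 11.5 points of average power at correlation 0.5, and is nearer 3 points if about half the effects are real. The sample size is unaffected, provided the week-12 WOMAC pain comparison is tested at the full 0.05 on which it was calculated.

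**What to change.** Replace the Bonferroni sentence under Data collection and statistical analysis with: *Multiple comparisons will be corrected by the Holm step-down Bonferroni procedure, keeping the family-wise two-sided error at 0.05.*

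Apply it to whichever non-primary comparisons the Bonferroni rule was meant for, using unadjusted p-values from the planned models. State that the single week-12 WOMAC pain comparison stays outside that family at two-sided 0.05. Without that statement, a family made up of the visits within WOMAC pain would take in the primary comparison.

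The cost is one sentence, with no new data and no change to the sample size or the primary test. The ordered thresholds can be worked out by hand or in a spreadsheet from SPSS output. Confidence intervals would be reported unadjusted or at the Bonferroni level and labelled accordingly, because they will not always agree with the Holm decisions. The change should be made before allocation is unblinded.
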